#### Reliability of Pupillometry in Preschoolers

We showed the feasibility of our methodology in early childhood by acquiring longitudinal pupillometric data in an eye-tracking battery of neurocognitive tasks in 100+ preschool children. Two cross-sectional analyses have been published [79,80], while a longitudinal study applied pupil responses as a mediating mechanism in early intervention outcomes [5]. We assessed the reliability of pupillometry in 26 participants with 3 measurements (baseline, after 6 months, and after 12 months). BPS showed high correlations between measurement time points (*r*s=0.69−0.81) and an intraclass correlation of ICC=0.90, 95% CI 0.83-0.95. SEPR showed lower correlations between measurement time points that might be induced by intervention effects.

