### Sample Size and Power

Sample sizes (n) were determined based on recruitment feasibility and the ability to detect moderate effects with a power of *β*>.80. For each task, we estimated the power by Monte Carlo simulations (k=1000) within respective models [97,98]. In the following sections, the sample size and power are reported, respectively, for each specific objective or task.

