### Work Package 1 (Objective 1): Validation of a Pupillometric Battery of LC-NE Functioning

#### Participants

We will recruit 90 preschool-aged children to participate in a passive pupillometry test battery designed to measure LC-NE activity.

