#### Sample Size and Power

A power analysis using a linear mixed model (LMM) indicates a power of *β*=.82 for 90 participants to detect a moderate stimulus effect (b=0.3) in the auditory oddball task (100 trials, 20% oddballs).

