### Statistical Analysis Plan

We will validate the pupillometric indices by a multitrait-multimethod design. In a homo-method analysis, the BPS and SEPR during the auditory oddball task (Figure 5A) will be compared to BPS and SEPR in tasks of LC-NE functioning with irregularity in rapid sound sequences [24] (Figure 5B), a visual oddball task [91] (Figure 5C), and an audio-cued visual search [92] (Figure 5D).

In a hetero-method analysis, the BPS and SEPR during the auditory oddball task will be compared to event-related potentials (ERPs) in concurrent EEG. We investigate oddball ERPs that are likely associated with LC-NE activity (P300, MMN) [27,100]. Finally, the pupillometric measures will be compared to divergent measures of cognitive and language ability as assessed by WPPSI-IV [93]. Patterns of high intercorrelations will be used to create a concise pupillometric battery of LC-NE functioning (~15 min). BPS and SEPR are reliably assessed in few oddball trials (k=20).

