##### Sample Size and Power

For the core longitudinal study with a cross-lagged panel model, power is *β*=.82 for 300 participants to detect a moderate cross-lagged effect of LC-NE functioning on psychopathology (a=0.2; see Figure 6).

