## Discussion

### Principal Findings

The LOCUS-MENTAL protocol outlines a longitudinal study design with the primary aim to establish LC-NE functioning as a neurobiological predictor of later psychopathology in childhood. We anticipate that the validation phase (Objective 1) will demonstrate convergent and discriminant validity of the pupillometric markers BPS and SEPR with sufficient reliability. By developing and validating a child-friendly, pupillometry-based tool, this aims to bridge a critical gap between neurobiological mechanism and clinical risk prediction, which is based solely on behavioral observation. Accordingly, this is a prerequisite to ensure the method sensitivity and specificity. This would provide a concise test battery that assesses a neurobiological mechanism that could be implemented in future clinical studies capturing a potential biomarker of psychopathology in early childhood. Furthermore, we hypothesize that BPS and SEPR will cross-sectionally differentiate between transdiagnostic risk profiles, such as irritability and behavioral inhibition, and serve as a mediator between childhood adversity and psychopathology (Objective 2). This would provide an underlying neurobiological basis for temperament dimensions that are also based on caregiver reports. In the longitudinal data, as a core outcome, we expect to reveal baseline LC-NE functioning at age 4‐6 years to predict the development of psychopathology at school age (Objective 3). This central component of the LOCUS-MENTAL project would provide causative evidence for an impact of LC-NE functioning on transdiagnostic mental health conditions. These findings will be used in forming a normative model as a pupillometry-based risk prediction tool, establishing a key neurobiological susceptibility mechanism that mediates the impact of early adversity on psychopathology (Objective 4). This will allow a translation of the experimental findings to clinical practice. For example, children associated with an elevated risk for psychopathology based on LC-NE functioning could be supported by evidence-based treatments that are effective before the onset of a mental health condition. This would emphasize a targeted prevention approach. We conclude that the identification of a neurobiologically grounded risk marker could transform our mental health infrastructure from interventions that are applied years after the onset of mental health problems to early and targeted support. Ultimately, this aims to reduce the lifetime burden of mental health problems.

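### Work package 1 expects the pupil indices to prove reliable, but its described analysis estimates no reliability and judges validity and selects the battery from raw correlations

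*Protocol article*

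**What the plan says.** The Statistical Analysis Plan of Work Package 1 describes a multitrait-multimethod comparison. BPS and SEPR from the auditory oddball task are set against the same indices in three other tasks, against concurrent EEG potentials, and against WPPSI scores as the divergent measure. The selection rule is: "Patterns of high intercorrelations will be used to create a concise pupillometric battery of LC-NE functioning". The same paragraph then states as fact that both indices are measured reliably with 20 oddball trials. It gives no coefficient.

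Under Expected Outcome and Study Hypotheses, convergent validity is to be read from moderate-to-high correlations of auditory oddball SEPR with the pupil measures in the other tasks. In the Discussion, the authors anticipate that this phase "will demonstrate convergent and discriminant validity of the pupillometric markers BPS and SEPR with sufficient reliability".

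The only earlier reliability figures are for BPS: correlations of 0.69 to 0.81 between time points and an ICC of 0.90, in 26 participants measured at baseline, 6 and 12 months. For the other index the text says only: "SEPR showed lower correlations between measurement time points that might be induced by intervention effects".

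The sample is 90 children. The power quoted for it, .82 from a linear mixed model, concerns a different quantity from the correlations, namely the ability "to detect a moderate stimulus effect (b=0.3) in the auditory oddball task (100 trials, 20% oddballs".

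**The concern.** An observed correlation between two scores mixes the true association with the reliability of both. Without the reliabilities, a weak convergent correlation cannot be told apart from a noisy measure. A weak correlation with WPPSI, which the plan would read as divergent validity, can arise from the same noise.

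This matters most for SEPR. It carries the convergent hypothesis, it has no reliability figure, and it rests on few event trials. The auditory oddball task is the fixed reference and is required for inclusion in the analysis, so noise in its SEPR would lower every convergent correlation at once. The battery chosen here is reused in Tasks 2.1, 2.2 and 3.1, so a task kept or dropped for the wrong reason stays that way through the longitudinal study.

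**Working it through.** **1. The plan's own figure.** The .82 for 90 children is a power for the oddball-versus-standard contrast. The simulated model cannot be rerun exactly, because alpha, the variance components and the scale of b are not stated. At two-sided alpha 0.05 (assumed), a paired effect of 0.3 with n=90 gives 0.80 (noncentral t) or 0.81 (normal), so .82 is attainable.

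This power says nothing about reliability. With residual SD 1 and 20 and 80 trials, the error variance of one child's contrast is 1/20 + 1/80 = 0.0625.
- Between-child slope SD 0.25: reliability 0.0625/(0.0625+0.0625) = 0.50; power about 1.00.
- Between-child slope SD 0.95: reliability 0.9025/(0.9025+0.0625) = 0.94; power 0.83.

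High power for the mean contrast can go with poor reliability of individual differences.

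**2. Event trials per task with complete data** (from the task descriptions).
- Auditory oddball: 100 × 0.20 = 20.
- Visual oddball: 72 × 0.20 = 14.4, about 14.
- Regular-to-irregular transition: 10.
- Cued visual search: 30 × 0.50 = 15.

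Only the auditory task reaches the 20 for which reliability is asserted. The missing-data text excludes children with per-task data validity below 50%. If that percentage counts trials (an assumption), a retained child could have 5 transitions. These counts concern SEPR. BPS is taken on every trial: 100, 72, 40 (2 × 5 + 3 × 10) and 30.

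**3. Attenuation.** Observed r = true r × √(rel₁ × rel₂). With equal reliabilities (assumed) and true r = .6:
- reliability .9: .6 × .9 = .54
- reliability .7: .6 × .7 = .42
- reliability .5: .6 × .5 = .30

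Read backwards, an observed .30 fits a true .6 at reliability .5 or a true .33 (.30/.9) at reliability .9. Sampling error adds to this: by Fisher z, an observed .30 has a 95% interval of .10 to .48 at n=90, and .07 to .50 at n=72, the lower bound of the planned completion rate (90 × 0.80).

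**4. Illustration of trial count.** Assume SEPR reliability of .5 to .8 at 20 trials and apply Spearman-Brown, rel(k) = m·rel/(1+(m−1)·rel), with m = k/20.
- k=14, m=.7: .35/.85 = .41 to .56/.76 = .74
- k=15, m=.75: .375/.875 = .43 to .60/.80 = .75
- k=10, m=.5: .25/.75 = .33 to .40/.60 = .67

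A true convergent r of .6 with the auditory task then appears as:
- transitions: .6 × √(.5 × .33) = .24 to .6 × √(.8 × .67) = .44
- visual oddball: .6 × √(.5 × .41) = .27 to .6 × √(.8 × .74) = .46
- cued search: .6 × √(.5 × .43) = .28 to .6 × √(.8 × .75) = .46

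For WPPSI, with assumed reliability .85 and a true r of .4, auditory SEPR would show .4 × √(.5 × .85) = .26 to .4 × √(.8 × .85) = .33.

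Spearman-Brown assumes interchangeable trials. Brief tones, six-second sequences, circles and search displays are not interchangeable, so these ranges show direction and rough scale only.

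**The case against.** The Discussion sentence is an expectation and not a commitment, and Objective 1 itself names only convergent and discriminant validity. A condensed article may leave the choice of reliability coefficient to a fuller plan, and a classical multitrait-multimethod matrix carries reliabilities on its diagonal. These points soften the concern but do not remove it: the article states reliability as fact, expects it as a finding, gives a selection rule based on correlations alone, and describes no analysis that would produce the coefficient.

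Selecting on raw correlations also has a defence. A noisy task would tend to show low convergent correlations and be dropped, and Work Package 4 predicts individual risk from measured scores, so penalising noise is reasonable. Disattenuated correlations can favour noisy tasks. This stands, and it is why corrected values should only be supportive. It does not help when the noise lies in the reference task.

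The count of 15 for the search task can also be questioned, because the hypothesis on SEPR before target detection is not limited to cued trials.

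A reader might go further and infer that the Task 3.1 power, stated "for 300 participants to detect a moderate cross-lagged effect of LC-NE functioning on psychopathology (a=0.2; see Figure 6", is overstated for SEPR. The documents do not support that. Nothing says this power was calibrated to the stability of BPS, and no SEPR reliability is given from which to recompute it. The earlier data are 6- and 12-month stability in 26 children with possible intervention effects, which is not within-session reliability. Task 2.2 uses latent constructs and the Figure 6 caption lists measurement errors, so shrinking a single observed score would be the wrong calculation. Nor do the documents show that SEPR is unreliable; they leave its reliability unknown.

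**Conclusion.** The concern holds as a gap in the Work Package 1 analysis. Reliability is asserted and expected but not estimated, while validity and battery selection are read from raw correlations. The direction of the effect is certain: unequal reliability changes which correlations look high or low. Its size is not, because no SEPR reliability is given. Under assumed equal reliabilities of .9 to .5, a true .6 shows as .54 to .30. Under the task-specific illustration it shows as .24 to .46. No stated power figure is called into question by this point.

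**What to change.** Add to the Work Package 1 Statistical Analysis Plan a within-session split-half reliability (Spearman-Brown), with confidence interval, for BPS and SEPR in each task. Report it beside the raw convergent and divergent correlations, and give disattenuated correlations with intervals as supportive. State that reliability will be considered before a task is called non-convergent or discriminant, and before the battery is fixed for T1.

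No new data are needed, because both indices are recorded on every trial and 82 of the 90 children had been assessed by February 2026. The validation analysis is planned for March 2026 and the longitudinal study for April 2026, so the change belongs before that analysis. The cost is a little extra analysis and wider intervals for the corrected correlations.

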**Figure 5. F5:**
[figure not shown]
Experimental tasks. (**A**) Auditory oddball task (see description above). (**B**) Irregularity in rapid sound sequences; sequences either have a pattern (regular=REG), have no pattern (irregular=IRR), or change regularity within the sequence (REG to IRR, IRR to REG). (**C**) Visual oddball task. (**D**) Cued and uncued visual search task. IRR: irregular; REG: regular.

### Expected Outcome and Study Hypotheses

A successful task manipulation will be indicated by a higher SEPR in oddball versus standard trials (ie, sensory selectivity) and declining BPS across standard trials (ie, habituation). We expect convergent validity with moderate-to-high correlations between the auditory oddball SEPR and the pupillometric measures in the validation tasks (including SEPR to a change from regularity to irregularity, SEPR to visual oddball stimuli, and SEPR before target detection). We expect convergent validity in the hetero-method analyses, whereas we expect divergent validity with cognitive and language development.

### Risk Assessment

We only include paradigms that are feasible in young children. This shall ensure a sufficient completion rate in preschoolers (>80%). The concurrent presentation of visual stimuli to maintain attention during the auditory oddball task may impede the SEPR. However, we recently showed in independent data that visual presentation during an auditory oddball task still induces distinct task-evoked pupillary responses.

### Work Package 2 (Objective 2): Association of LC-NE Functioning With Correlates of Psychopathology

#### Task 2.1: LC-NE Functioning Corresponds to Early Dispositional Risks for Psychopathology

##### Participants

A sample of 140 preschool-aged children will be recruited in accordance with the general recruitment strategy of the study.

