**Figure 4. F4:**
[figure not shown]
LOCUS-MENTAL study design with task integration. The flowchart illustrates the longitudinal study design consisting of a pilot phase and 3 primary assessment waves (**T1, T2, AND T3**) each one year apart. Each assessment wave spans over 2 years. The longitudinal study will follow a cohort of 300 preschool children (initially aged 4‐6 years). Dark blue boxes indicate longitudinal study elements, and light blue boxes indicate cross-sectional tasks within the longitudinal study. Dotted lines indicate selection of a specific subsample at specific time points, including a randomized subsample (n=160) either from T2 or T3 for Task 3.2. Small “n” represents the subsample number, while “N” represents the primary study sample.

**Table 1. T1:** Assessment measures and questionnaires of LOCUS-MENTAL.

Modality, instrument and task		Construct	Objective
Questionnaires (caregiver)	
core set		Demographic data	1.1.‐3.2
CBCL^a^ [4-18,82]		Psychopathology	2.1‐3.2
BIQ^b^ [83]		Behavioral inhibition	2.1‐3.2
ARI^c^ [84]		Irritability	2.1‐3.2
CBQ-VSF^d^ [85]		Temperament	2.1‐3.2
ACE+^e^ [86]		Childhood Adversity	2.2‐3.2
F-SoZu 6^f^ [87]		Social support	2.2‐3.2
Interview (child)	
CLES-P^g^ [88]		Childhood adversity	2.2‐3.2
VEX-Preschool^h^ [89]		Violence exposure	2.2‐3.2
Pupillometry battery	
Auditory oddball [90]		LC-NE activity	1.1‐3.2
Visual oddball [91]		LC-NE activity	1.1‐3.2
Cued visual search [92]		LC-NE activity	1.1‐3.2
Rapid sound sequences [24]		LC-NE activity	1.1‐3.2
Cognitive tests	
WPPSI^i^ subtest–vocabulary [93]		Verbal IQ estimate	1.1‐3.2
WPPSI subtest–block design [93]		Nonverbal IQ estimate	1.1‐3.2
Bio samples	
Hair sample		Retrospective cortisol level	2.2‐3.2
Saliva sample		Acute cortisol level	2.2‐3.2
Assessment	
Child stress test [94]		Stress reaction	3.2
EEG^j^	
See pupillometry tasks		LC-NE activity	1.1‐2.1
Go/NoGo Task [50]		Error Related Negativity (ERN)	2.1
Neurocognitive tasks	
Dot-probe tasks [95]		Irritability	2.1
Frustrative reward learning task [96]		Irritability	2.1

a CBCL: Child Behavior Checklist

b BIQ: Behavioral Inhibition Questionnaire

c ARI: Affective Reactivity Index

d CBQ-VSF: Children’s Behavior Questionnaire–Very Short Form

e ACE+: Adverse Childhood Experiences Questionnaire Plus

f F-SoZu 6: Social Support Questionnaire

g CLES-P: Childhood Life Events Scale–Preschool

h VEX-Preschool: Violence Exposure Scale–Preschool

i WPPSI: Wechsler Preschool and Primary Scale of Intelligence

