##### Sample Size and Power

A power analysis based on an LMM indicates that a sample of 140 participants provides power of *β*=.84 to detect a moderate correlation (b=0.3) between LC-NE functioning and dispositional risks.

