##### Expected Outcome and Study Hypotheses

Behavioral inhibition (BIQ score) is expected to correlate positively with both BPS and SEPR in the pupillometric battery of LC-NE functioning. In contrast, irritability (assessed via ARI score) is expected to show differential profiles of LC-NE functioning. We expect high irritability scores and high SEPR to be associated with higher internalizing symptoms, while high irritability scores and low SEPR will be associated with higher externalizing symptoms—these expected outcomes are supposed to match ERN profiles [101]. Furthermore, in the neurocognitive paradigms, participants with high-irritability-low-SEPR profiles are further expected to show increased attentional bias toward threat cues (threat perception) and decreased attentional shifts during frustration (frustrative reward learning). These patterns would suggest a subgroup with elevated risk for conduct disorders. We will further explore LC-NE functioning in children with both high irritability and high behavioral inhibition, who are expected to exhibit higher negative emotionality and an increased BPS as an index of an elevated LC-NE tonic activity.

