##### Risk Assessment, Participant Burden, and Ethical Considerations

This task is associated with the highest participant burden due to its combined EEG assessments and neurocognitive task demands. To mitigate this, we will provide additional breaks for the participants and offer food and drinks between assessments. We assume a higher attrition rate for this task compared to other tasks, estimated at approximately 30%. Thus, this task is designed as more optional, ensuring that potential dropouts will not compromise subsequent study objectives.

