The LOCUS-MENTAL study uses targeted strategies across its work packages to manage missing data and ensure robust longitudinal findings. Work package 1 focuses on feasibility measures by using passive and child-friendly paradigms to achieve a projected completion rate of over 80%. Statistical analysis will exclude children that have per-task data validity rates of less than 50% or more than one missing task. The auditory oddball task is a marker task that is required to be included in the statistical analysis. We established standardized procedures of pupillometry data preprocessing to address within-trial missing data due to inattention. Work package 2 addresses high-burden EEG assessments by designating them as “more optional” in the context of the overall project, which allows for an expected 30% attrition rate without hindering subsequent study objectives. For the longitudinal assessments in work package 3, the study implements retention strategies like online data collection and locator documents. In addition, the statistical framework of work package 3 includes LMM and structural equation modeling to handle intermittent missingness across time points. Questionnaire data on an item level with per-measure missing rates up to 20% will be addressed by Multiple Imputation by Chained Equations (MICE) that preserves statistical power under the missing at random assumptions. However, children with increased irritability or increased burden may be more likely to drop out (ie, missing not at random or MNAR). Thus, pattern mixture models will be applied as a sensitivity analysis to determine if the developmental trajectories of LC-NE functioning are biased by specific attrition patterns. In addition, Inverse Probability Weighting (IPW) in the longitudinal data analysis can be used to adjust for non-random attrition by weighting the remaining participants based on baseline characteristics (eg, socioeconomic status or initial psychopathology scores) that predict dropout. Missing bio samples will be addressed by case-wise exclusion in the specific subanalysis. Finally, work package 4 uses v-fold validation to evaluate the predictive stability of the risk prediction tool.

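### Task 2.1 plans temperament hypotheses that need no EEG in 140 children, although Table 1 lists all their measures for the 300-child cohort

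*Protocol article*

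**What the plan says.** All places are in the Protocol article.

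- **Sample and power.** Task 2.1, Participants: "A sample of 140 preschool-aged children will be recruited in accordance with the general recruitment strategy of the study". Task 2.1, Sample Size and Power, based on a linear mixed model (LMM): "a sample of 140 participants provides power of *β*=.84 to detect a moderate correlation (b=0.3"). The general Sample Size and Power section adds that "we estimated the power by Monte Carlo simulations (k=1000) within respective models". It gives no alpha, sidedness or variance components.
- **Burden and loss.** The Task 2.1 risk assessment ranks this task as the most demanding, because of EEG and the neurocognitive tasks, and expects about 30% attrition. It concludes: "Thus, this task is designed as more optional, ensuring that potential dropouts will not compromise subsequent study objectives".
- **Hypotheses.** Task 2.1 expects the BIQ score to correlate positively with BPS and SEPR. For irritability (ARI) it states: "We expect high irritability scores and high SEPR to be associated with higher internalizing symptoms", with low SEPR pointing to externalizing symptoms. These profiles are then linked to ERN, threat bias and frustration.
- **Schedule.** Table 1 lists BIQ, ARI and CBCL for objectives 2.1 to 3.2 and the pupillometry battery for 1.1 to 3.2. Go/NoGo (ERN), dot-probe and frustrative reward learning are listed for 2.1 only. Tasks 2.2 and 3.1 use 300 children. The Figure 4 legend says "light blue boxes indicate cross-sectional tasks within the longitudinal study".
- **Missing data.** The missing-data paragraph under Ethical Considerations says "children with increased irritability or increased burden may be more likely to drop out". It assigns pattern mixture models to developmental trajectories and inverse probability weighting to the longitudinal analysis. It names no such adjustment for Task 2.1.

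**The concern.** The two lead hypotheses of Task 2.1 use only pupillometry and caregiver questionnaires, yet they are planned in the sample built around the most demanding session. If Table 1 is taken at face value, the same variables exist for about twice as many children. Confining these models to 140 gives up precision for no stated reason.

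The protocol's safeguard is that losses here will not harm later objectives. That does not protect Task 2.1, which is a named part of Objective 2. Irritability is also both the predictor under study and one of the characteristics the protocol associates with possible dropout. If that dropout occurs, the children with high irritability and low SEPR, whom the task wants to characterize, could be thinned out.

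**Working it through.** **1. Which hypotheses need the EEG/neurocognitive session?**

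| Hypothesis | Measures | Objectives in Table 1 |
|---|---|---|
| BIQ with BPS and SEPR | BIQ; battery | 2.1–3.2; 1.1–3.2 |
| ARI with SEPR on CBCL internalizing/externalizing | ARI, CBCL; battery | 2.1–3.2; 1.1–3.2 |
| Match to ERN profiles | Go/NoGo EEG | 2.1 only |
| Threat bias, frustration | Dot-probe, frustrative reward | 2.1 only |

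Only the first two rows can move to the larger cohort. The Task 2.2 text itself confirms the battery and the CBCL in the 300. BIQ and ARI in the 300 rest on Table 1 alone.

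**2. The plan's own power figure.** The LMM cannot be rebuilt from what is given. A simple correlation of 0.3, two-sided 5% (assumed), with power = Φ(atanh(r)·√(n−3) − 1.960), gives:

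- n=140: 0.3095 × √137 = 3.623, minus 1.960 = 1.663, power .952
- n=98: 0.3095 × √95 = 3.017, minus 1.960 = 1.057, power .855

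The stated .84 is not reproduced at 140 and is close to the result at 98. Since 98/(1 − 0.30) = 140, the figure may already describe completers, although the text attaches it to 140. Other unstated settings also land near .84 at n=140 (r=0.25 gives .848; alpha 0.01 gives .852). The figure can be neither confirmed nor called wrong.

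**3. Precision, independent of the power figure.** The standard error scales as 1/√n.

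- 300 against 140: √(140/300) = 0.683, about 32% smaller
- 240 (80% of 300 usable, assumed) against 140: √(140/240) = 0.764, about 24% smaller
- 300 against 98 (140 × 0.70): √(98/300) = 0.572, about 43% smaller. This is an upper bound: it applies the 30% loss to the non-EEG measures and takes no loss off the 300.
- 240 against 98: √(98/240) = 0.639, about 36% smaller

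For an observed correlation of 0.3, the 95% confidence interval is 0.108 to 0.470 at n=98, 0.141 to 0.444 at n=140 and 0.193 to 0.400 at n=300. The half-widths are about 0.18, 0.15 and 0.10.

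**4. Power, if .84 refers to 140 analysed children (two-sided 5% assumed).** The implied noncentrality is 1.960 + 0.994 = 2.954.

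- n=98: 2.954 × √(98/140) = 2.472, minus 1.960 = 0.512, power about .70
- n=300: 2.954 × √(300/140) = 4.324, minus 1.960 = 2.364, power about .99

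**5. Selection.** The protocol gives no rate of dropout by irritability, so no size can be attached to range restriction or bias.

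**The case against.** Five points can be made for the plan.

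- **Table 1 may not be a whole-cohort schedule.** It lists hair and saliva samples for 2.2 to 3.2, while the text places their collection in Task 3.2, a subsample of 160. The Task 2.2 and 3.1 texts name only the CBCL and adversity as behavioral measures. This stands: collection of BIQ and ARI in all 300 must be confirmed first. That the 140 lie within the 300 is also inferred. The Figure 4 legend supports it, as does Work Package 4, which gives the full sample from Work Packages 2 and 3 as the 300 children of Task 2.2.
- **The 30% may concern the EEG only.** The missing-data paragraph ties it to the EEG assessments, so a child who declines EEG could still supply pupillometry and questionnaires. This stands: 98 need not be the sample size for these two hypotheses.
- **A power failure is not shown.** A reader might infer that power falls to .70. That follows only if .84 means 140 analysed children, and the simple formula gives .855 even at 98.
- **Irritable children are not shown to be selected out.** A reader might infer that they are, but the protocol says only that they may be more likely to drop out, gives no size, and says this just after discussing missingness across time points.
- **The hypotheses form a linked set.** Testing them in children who have ERN and task data as well is coherent, and a supplementary analysis in the larger cohort is not forbidden. That justifies keeping the linked analyses in the subsample. It does not explain why the stand-alone BIQ and ARI models should be confined to it.

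**Conclusion.** The point holds as an avoidable loss of precision, limited to the BIQ–BPS/SEPR and ARI-by-SEPR models. It does not extend to the ERN, dot-probe and frustrative-reward hypotheses, which need the subsample.

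The main figure is a standard error about 32% smaller at 300 than at 140, or about 24% smaller if 240 of the 300 are usable and all 140 are. The 43% gain over 98 and the power contrast of .70 against .99 are conditional and should be quoted only with their conditions. Everything rests on Table 1 being right that BIQ and ARI are collected beyond Task 2.1.

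Selection on irritability is a relevant risk, because irritability is the predictor and no adjustment is named for this task. The document does not support calling it a bias, or calling Task 2.1 underpowered.

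**What to change.** 1. State in the Task 2.2 and 3.1 measures that BIQ and ARI are collected in all T1 children, as Table 1 indicates, and state whether the 140 are part of the 300.
2. In Task 2.1, specify that the BIQ–BPS/SEPR and ARI-by-SEPR models (CBCL internalizing and externalizing) are run in all T1 children with valid pupillometry and questionnaires, planned n=300.
3. Keep the ERN, dot-probe and frustrative-reward analyses in the n=140 subsample. There, compare completers with non-completers on T1 ARI, BIQ and CBCL, and add weighting for completion as a sensitivity analysis.
4. State whether the power of .84 refers to 140 recruited or 140 analysed children, and at which alpha.

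The cost is protocol wording and models run on a larger data set, with no extra visits if Table 1 is the true schedule. If BIQ and ARI are not in fact planned for all 300, the cost is two added caregiver questionnaires. The main downside is timing: these Task 2.1 results would wait until T1 is complete for the full cohort.
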